#### Acceptability Benchmarks

Acceptability will include dimensions of usability from the System Usability Scale [65]. We also created additional single-item questions, drawing upon the Technology Acceptance Model [66], evaluating overall satisfaction, engagement, visual appeal of content, understandability of program content, desire to continue the program, perceived skill acquisition, perceived confidence in implementing skills, and perceived helpfulness of *CBT-based Mindful Courage*. Participants in the *CBT-based Mindful Courage*+coached self-monitoring condition will rate their responses to each item from 1 (*strongly disagree*) to 5 (*strongly agree*). Given that this is the first pilot feasibility trial of *CBT-based Mindful Courage*, and our primary intention is to evaluate whether this intervention has preliminary promise for acceptability, benchmarks for these items will be conservatively set to an average score of >3.5 (*agree)*.

#### ED-Related Outcomes

BED-related outcomes, examined on an exploratory basis to estimate effect sizes for a full-scale RCT, will include (1) frequency of binge eating episodes in the last 28 days, which will be assessed with the Eating Disorder Examination Questionnaire (EDE-Q) [50]; and (2) ED symptoms, assessed with the global EDE-Q score. Additional outcomes will include (3) changes in clinical impairment measured via the Clinical Impairment Assessment [51] and (4) depressive symptoms measured via the 9-item Patient Health Questionnaire-9 [52]. All these measures have demonstrated adequate psychometric properties [51,67-72].

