We developed a digital treatment combining CBT and mindfulness training for BED, called *CBT-based Mindful Courage.* We will conduct a small-scale randomized controlled trial (RCT) to assess the feasibility and acceptability of *CBT-based Mindful Courage*. The primary goals are to (1) evaluate feasibility, including intervention and assessment completion; and (2) evaluate acceptability, including dimensions of usability, overall satisfaction, engagement, visual appeal of content, understandability of program content, desire to continue the program, perceived skill acquisition, perceived confidence in implementing skills, and perceived helpfulness. Notably, the study is funded by the National Center for Complementary and Integrative Health (NCCIH) and guided by the NCCIH research framework [33] and the National Institutes of Health stage model for intervention development [34]. Accordingly, we will not conduct between-group analyses at this stage of development. Instead, we will evaluate within-treatment-condition mean changes in outcomes (binge eating frequency, ED symptoms, clinical impairment, and depression) and mechanisms (emotion dysregulation, dietary overrestriction, and trait mindfulness) as exploratory objectives.

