#### Mechanisms

We will measure mechanisms of change due to the intervention on an exploratory basis. This will include (1) emotion dysregulation, measured via the Difficulties in Emotion Regulation Scale-Short Form [53]; (2) dietary overrestriction, measured via the restraint subscale of the EDE-Q [50]; and (3) trait mindfulness, measured via the Cognitive and Affective Mindfulness Scale-Revised [54]. All these measures have demonstrated adequate psychometric properties [54,67,73].

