#### Outcomes and Mechanisms

On an exploratory basis, we will evaluate changes in outcomes and mechanisms from baseline to each subsequent assessment point using linear mixed models, separately for participants in each of the conditions (n=20 in each condition). Mixed models enable the inclusion of all participants regardless of missing data (ie, an intent-to-treat analysis). We will also calculate Cohen *d* effect sizes for changes within condition.

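### The exploratory outcomes are meant to supply effect sizes for a full-scale trial and mechanism change attributed to the intervention, but the within-arm analysis planned does not identify either

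*Protocol article*

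**What the plan says.** All of this is in the protocol article.

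- **ED-Related Outcomes (Measures):** binge frequency and global EDE-Q score are "examined on an exploratory basis to estimate effect sizes for a full-scale RCT".
- **Mechanisms (Measures):** "We will measure mechanisms of change due to the intervention on an exploratory basis". The measures are emotion dysregulation, dietary restraint and trait mindfulness.
- **Introduction, last paragraph:** citing the funder's framework and the NIH stage model, "we will not conduct between-group analyses at this stage of development". Instead, "we will evaluate within-treatment-condition mean changes in outcomes" and mechanisms.
- **Outcomes and Mechanisms (Statistical Analysis):** linear mixed models are fitted separately in each arm of 20, and Cohen d is to be calculated as "effect sizes for changes within condition".
- **Overview of Coached Self-Monitoring and Treatment Conditions:** both arms self-monitor food intake and receive weekly coaching calls. The intervention arm adds the digital program.
- **Future Directions:** the project may serve as the foundation for a full-scale efficacy RCT.

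No section plans an arm-by-time term, a between-arm difference or a mediation model.

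**The concern.** Two stated purposes do not match the stated analysis. The effect size that a two-arm efficacy trial needs is the difference between arms, and the plan excludes that quantity. What it will produce is change from baseline within each arm. In the intervention arm that change contains at least four parts: the digital program, the self-monitoring and coaching that the control arm also receives, the natural course of the disorder, and regression to the mean, since entry requires current binge eating disorder. Without the concurrent contrast these parts cannot be separated. For the same reason the data cannot attribute change in a mechanism measure to the intervention.

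At stake is the planning of the next trial. A reader who takes the protocol at its word would expect a usable effect size from this pilot and would find only within-arm figures, which for an active program are likely to exceed the between-arm effect whenever the control arm also improves.

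**Working it through.** **No figure to reproduce.** The sample size of 40 rests on pragmatic grounds, and the protocol gives no alpha, power, effect size or SD. The effect sizes below are therefore assumptions, used to show how little a within-arm d constrains the between-arm effect.

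**Step 1. What within-arm d leaves open.** Put both arms' changes on one common SD. Then

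between-arm d = within-arm d (intervention) − within-arm d (control).

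Assume 1.0 in the intervention arm and let the control arm vary. By the normal approximation, with two-sided 5% and 80% power, n per arm = 2(1.96 + 0.84)²/d² ≈ 15.7/d². Taking d = 1.0 as if it were the between-arm effect gives 16 per arm. Power at 16 per arm is approximately Φ(d·√(16/2) − 1.96).

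| Control within-arm d (assumed) | Between-arm d | n per arm needed | Power at 16 per arm |
|---|---|---|---|
| 0.0 | 1.0 | 16 | 81% |
| 0.2 | 0.8 | 25 | 62% |
| 0.5 | 0.5 | 63 | 29% |
| 0.8 | 0.2 | 393 | 8% |
| 1.0 | 0.0 | no finite n | not applicable |

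The same intervention-arm figure is compatible with every row. A second assumed case, by the two-sample t calculation: within-arm d of 0.9 and 0.5 give a between-arm d of 0.4. Sizing on 0.9 gives 21 per arm (20.4 before rounding), sizing on 0.4 gives 100 (99.1), and power at 21 per arm with a true 0.4 is 24%.

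**Step 2. What a between-arm estimate would deliver here.** The approximate 95% half-width of an unadjusted standardized difference near zero is 1.96·√(2/n). The n come from the target sample size and the Feasibility Benchmarks section, assuming equal retention by arm.

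| Stage | n per arm | Half-width (SD) |
|---|---|---|
| All randomized | 40/2 = 20 | 1.96·√(2/20) = 0.62 |
| End of treatment, 75% (30/40) | 30/2 = 15 | 1.96·√(2/15) = 0.72 |
| Follow-up, 65% (26/40) | 26/2 = 13 | 1.96·√(2/13) = 0.77 |

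Baseline adjustment would change these widths by an amount that the documents do not allow one to compute. The difference can be estimated, but an interval of this width spans most of the effects in the first table.

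**Step 3. Attribution of mechanism change.** The Mechanisms section credits the change to the intervention. The only analysis offered is change from baseline in each arm separately. Without a control contrast, that sentence has no analysis behind it.

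**The case against.** **These aims are exploratory.** The protocol says so repeatedly, and the primary aims do not depend on them. This stands and limits the weight of the point. It does not turn a within-arm change into an estimate of a between-arm effect.

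**A pilot need not compare arms.** Leaving out between-group testing is defensible, and the protocol ties the choice to its funder's framework. This also stands. The fault lies in the purpose given to the analysis, not in the absence of a test.

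**Both arms are summarized, so a planner could subtract.** Partly true: the inputs for a rough contrast will exist. But that subtraction is the comparison the Introduction excludes. It also requires a common standardizer, and no estimate or interval for the difference is planned.

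**A separate analysis plan may settle it.** This is not a gap left for another document. The article itself states purposes and an analysis that do not fit together.

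Four stronger readings are tempting, and the documents do not support them:

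- *The next trial will be sized on the intervention arm's d alone.* No section says so. The contrasts of 16 with 393 and 21 with 100 per arm show a possible misuse under assumed values, not a planned one.
- *The plan will read significance in one arm but not the other as an effect.* The analysis section states no significance criterion and no rule for comparing the arms.
- *The trial claims to demonstrate mechanisms.* The text speaks of measuring them on an exploratory basis, and the Discussion calls them potential mechanisms. The attribution is loose causal wording; no mediation claim is planned.
- *The pilot yields nothing for planning.* It will yield SDs, correlations between visits and retention.

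**Conclusion.** The point holds as a mismatch between stated purpose and planned analysis, confined to the exploratory aims, and it is of moderate severity. The conclusion that within-arm change does not identify the between-arm effect needs no assumed value: it follows from the exclusion of between-group analyses and from the components that both arms share. The sample-size figures rest on assumed effect sizes on a common SD and only illustrate scale. The half-widths of 0.62, 0.72 and 0.77 SD rest on the protocol's own numbers, with equal retention by arm and no covariate adjustment. They show that even a between-arm estimate from this trial should not by itself fix the size of the next one. Feasibility and acceptability are unaffected.

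**What to change.** **Minimum change, wording only.**

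1. In ED-Related Outcomes, replace the effect-size purpose with the planning quantities this trial can supply: SDs, correlation between visits and retention.
2. In Mechanisms, replace the attribution to the intervention with *change in potential mechanisms within each condition*.
3. In Outcomes and Mechanisms, state that within-arm changes are reported as estimates with 95% CIs.

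**If the effect-size purpose is kept.**

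1. Fit one model to both arms and report the baseline-adjusted between-arm difference in change with a 95% CI and no hypothesis test.
2. Amend the Introduction's exclusion of between-group analyses to match.
3. State that the unadjusted half-width is about ±0.62 SD at 20 per arm, ±0.72 at 15 and ±0.77 at 13, so the estimate is too imprecise to be the sole basis for sizing a full trial.

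**Cost.** Two or three sentences, or one additional model on data already being collected. No visit, measure or participant is added. The downside is a more modest claim. With results expected to be analyzed by May 2027, the change can be made before analysis.

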#### Mechanisms

We will measure mechanisms of change due to the intervention on an exploratory basis. This will include (1) emotion dysregulation, measured via the Difficulties in Emotion Regulation Scale-Short Form [53]; (2) dietary overrestriction, measured via the restraint subscale of the EDE-Q [50]; and (3) trait mindfulness, measured via the Cognitive and Affective Mindfulness Scale-Revised [54]. All these measures have demonstrated adequate psychometric properties [54,67,73].

#### Additional Measures

We will collect additional measures to be used in exploratory analyses. At baseline, we will collect data on duration of illness, past treatment experiences, past meditation experiences, and eating self-monitoring app use. We will also collect data on adverse events, positive and negative affect measured via the Positive and Negative Affect Schedule [55], savoring measured via the Savoring Beliefs Inventory [56], food craving measured via the Food Cravings Questionnaire-Trait-reduced [57], anxiety symptoms measured via the Generalized Anxiety Disorder-7 item assessment [58], body satisfaction measured via the Body Shape Questionnaire [59], binge eating symptoms measured via the Binge Eating Scale [60], and BMI derived from self-reported height and weight.

### Procedure

#### Screening

See Figure 2 for a graphic of the study timeline. Online advertisements will include a link for an online prescreening (via HIPAA-secured Qualtrics surveys). Interested participants can then use this link to be assessed for preliminary eligibility; this will include questions on age, ability to engage in the research study, and the Eating Disorder Diagnostic Scale [61]. If individuals meet preliminary eligibility based on the online prescreener, they will be invited to a complete a HIPAA-secured Zoom-based screening interview with a trained psychology student. The Zoom-based screening interview will include informed consent, administration of the Structured Clinical Interview for *Diagnostic and Statistical Manual of Mental Disorders, 5th edition* [49] to confirm BED diagnosis, and a semistructured interview-based assessment to evaluate inclusion and exclusion criteria (refer to the Measures section).

**Figure 2 figure2:**
[figure not shown]
Cognitive behavioral therapy (CBT)–based Mindful Courage timeline. Note: at baseline, participants are randomized to either (1) CBT-based Mindful Courage+coached self-monitoring or (2) coached self-monitoring.

#### Randomization and Baseline Session

If participants are eligible and willing to continue, they will be randomly assigned to either coached self-monitoring or *CBT-based Mindful Courage*+coached self-monitoring by the psychology student who completed the screening interview. Following our prior work [35], randomization will be achieved using a web-based computerized urn randomization program that ensures balance across treatment groups based on sex, age, binge eating severity, and race or ethnicity. Allocation concealment will be ensured because the program reveals assignments only after participant enrollment. After randomization, participants will proceed to the baseline study session (also conducted over Zoom by the psychology student; Multimedia Appendix 2) and will be instructed on how to track their food intake in *Recovery Record.* They will also receive the orientation for phone coaching. Participants randomized to the *CBT-based Mindful Courage*+coached self-monitoring condition will be instructed on how to access *CBT-based Mindful Courage* (either on their computers or via Android or iPhone) and will complete session 1 of the intervention as part of the visit. After completing session 1, participants will be informed that they will have 18 weeks of access to the app to complete 16 lessons and the 2 accompanying mindfulness practices, with weekly support from a student coach.

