### Study Design

This study is a 2-arm pilot feasibility RCT with parallel assignment and a 1:1 allocation ratio. All procedures reported here are derived from protocol version 1.0. Participants will be randomized to one of the following groups: (1) coached self-monitoring or (2) *CBT-based Mindful Courage*+coached self-monitoring. Participants will be blinded as to whether they received the active intervention or control condition. Outcome assessors and data analysts will be blinded to group allocation. All recruitment and study activities will be conducted online; the principal investigator and study staff will be located at Yeshiva University. Participants will complete interview-based and self-report assessments assessed at baseline, midtreatment, end-of-treatment, and 2-month follow-up on Health Insurance Portability and Accountability Act (HIPAA)–secured Zoom.

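### The baseline session comes after randomization and is run by staff who know the allocation, so the baseline behind all exploratory within-arm changes can be influenced by it.

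*Protocol article*

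**What the plan says.** All references are to the protocol article.

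- **Who assigns.** Under Randomization and Baseline Session, eligible participants are assigned "by the psychology student who completed the screening interview".
- **Order of events.** The same section continues: "After randomization, participants will proceed to the baseline study session (also conducted over Zoom by the psychology student". It cites Multimedia Appendix 2, the summary of measures, at that point.
- **When the arm becomes known.** Concealment is said to hold because "the program reveals assignments only after participant enrollment". The note to Figure 2 agrees that "at baseline, participants are randomized to either" arm.
- **What else happens at the visit.** Food tracking and coaching are explained. Intervention participants are then shown how to reach the program and "will complete session 1 of the intervention as part of the visit".
- **What baseline is for.** Study Design makes it one of the four assessment points: "Participants will complete interview-based and self-report assessments assessed at baseline, midtreatment, end-of-treatment, and 2-month follow-up". Outcomes and Mechanisms then models "changes in outcomes and mechanisms from baseline to each subsequent assessment point", separately in each arm, with Cohen d for change within arm. ED-Related Outcomes gives the purpose as effect sizes for a later full-scale trial.
- **Blinding.** Study Design states: "Outcome assessors and data analysts will be blinded to group allocation".

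**The concern.** A baseline is meant to describe the participant before anything that depends on the arm has happened. Here the person running the session already knows the arm, and the participant may know it too. Expectation or disappointment can colour self-report, and the student's handling of the session can differ by arm without intent.

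This matters more than usual because the plan makes no between-group comparison. Each arm's result is its own change from its own baseline, so a disturbed baseline goes straight into the reported change. Neither a larger sample nor a mixed model removes such a shift, because the model takes the baseline values as given. The resulting effect sizes are intended for planning the next trial, so an error would be carried forward.

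**Working it through.** There is no stated figure to reproduce. The check is one of order, personnel and use, followed by a short illustration of size.

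**1. Order.** The section on randomization runs: eligibility confirmed, assignment made, baseline session. The Figure 2 note also places randomization at baseline. Nothing in the shown text puts the outcome and mechanism questionnaires before the assignment. The urn program balances on binge eating severity, so some severity measure must exist beforehand, but it is not said to be the EDE-Q baseline that is analysed.

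**2. Personnel.** One sentence names the student who did the screening interview as the person who assigns. The next has the baseline session also run by the psychology student. The natural reading is that this is the same person. In any case, whoever gives the arm-specific instructions at that visit knows the arm.

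**3. Blinding.** Study Design counts baseline among the assessment points and says that assessors are blinded. For the baseline visit, the two statements do not fit together as written.

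**4. What depends on this baseline.** There are four outcomes (binge frequency, global EDE-Q, Clinical Impairment Assessment, PHQ-9) and three mechanisms (emotion dysregulation, EDE-Q restraint, trait mindfulness). With three later assessments and two arms, that gives 7 × 3 × 2 = 42 within-arm changes, resting on 7 × 2 = 14 baseline means.

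**5. What does not depend on it.** The feasibility benchmarks count people randomized, lessons done and later visits attended. The acceptability benchmarks are ratings by intervention participants. None uses a baseline score.

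**6. Size, as illustration only.** Let knowledge of the allocation shift the mean baseline by b SD, with follow-up unaffected. Standardized on the baseline SD,

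d = (follow-up mean − baseline mean) / SD, so d becomes d − b.

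For assumed b = 0.1, 0.2 and 0.3, d is off by 0.1, 0.2 and 0.3. The article does not name the standardizer. With the SD of the change, equal variances and a baseline–follow-up correlation r, the shift is b / √(2(1 − r)). That equals b at r = 0.5, is larger above that and smaller below it.

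**7. Could it be seen in the data?** The standard error of a baseline mean at n = 20 is 1/√20 = 0.22 SD. For the difference between two arms' baseline means it is √(1/20 + 1/20) = 0.32 SD. A shift in the assumed range would be hidden in sampling noise, so a baseline table could not rule it out.

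**The case against.** The other side has several good points.

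- **The affected results are exploratory.** This stands, and it limits the severity. The primary aims are feasibility and acceptability, and with no between-group analysis an arm-specific shift biases no planned comparison.
- **The analysed measures are questionnaires.** This largely stands. No named outcome or mechanism is rated by the student, and data are collected in Qualtrics. Binge frequency covers the past 28 days, so knowing the arm could alter only how episodes are reported. The participant's expectation and the student's handling of the session remain as routes.
- **Participants are said to be blinded to whether theirs is the active arm.** This helps somewhat, but intervention participants receive the program at this visit.
- **Multimedia Appendix 2 and Figure 2 may give the order within the visit.** Neither is shown. They could settle whether questionnaires precede session 1, but the text still places the whole session after randomization.

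A reader might also draw stronger conclusions that the document does not support:

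- *That session 1 contaminates the baseline.* The section narrates session 1 last. Its position relative to the questionnaires is unclear, not shown to be wrong.
- *That assessor blinding is contradicted throughout.* The section on later assessments does not say who conducts them, so blinded assessors there remain possible.
- *That allocation concealment fails.* The program reveals the arm only after enrollment. The issue is measurement after the reveal.
- *That participants will be lost between assignment and baseline.* Each would be 1/20 = 5% of an arm without a change score, but the text gives no interval between the two steps, and such loss is hypothetical.

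**Conclusion.** The point holds as a design weakness that should be fixed, confined to the exploratory results. As written, the baseline that anchors all within-arm changes and Cohen d values is collected after assignment, in a session run by someone who knows the arm. It can therefore be influenced by the allocation. For this one visit, the procedure also sits uneasily with the assessor-blinding statement.

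The size and direction of any bias are unknown. The 0.1 to 0.3 range is an assumption with no basis in the document, and its one-for-one effect on d requires an unaffected follow-up and standardization on the baseline SD. The conclusion itself needs only the stated order, the stated personnel and the stated use of baseline. It assumes that the outcome questionnaires are completed in the baseline session, which the citation of the measures appendix at that point supports. The feasibility and acceptability conclusions are untouched.

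**What to change.** 1. Reorder the visit: consent and eligibility; all baseline questionnaires completed and submitted in Qualtrics; urn program run and assignment revealed; orientation and, in the intervention arm, session 1.
2. Flag any participants already enrolled under the present order, so that the exploratory changes can be read with that in mind.
3. Reconcile Randomization and Baseline Session with the blinding statement in Study Design, saying which assessments are made by blinded staff.
4. If practice already follows this order, correct the text of Randomization and Baseline Session instead.

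The cost is small but not nil. A few eligible people may complete baseline and then not be randomized, which could slightly lower the benchmark of randomizing 75% of eligible people screened. With 40 randomized, that benchmark corresponds to 40/0.75 = 53.3 eligible screens. At 53 the rate is 40/53 = 75.5%, and at 54 it is 40/54 = 74.1%, so one such person matters only when the rate is already close to the line. Data collection is stated to have begun in November 2025, so early and later enrollees may also have followed different orders.

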**Inclusion criteria**
Aged 18 to 75 yearsAbility to speak English fluentlyMeeting *Diagnostic and Statistical Manual of Mental Disorders, 5th edition* criteria for current binge eating disorder (BED)Willing and able to commit to the entire study protocol

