#### Feasibility Benchmarks

Benchmarks for feasibility are based on previous digital interventions for EDs [31,62-64], and include (1) feasibility of recruitment (40 participants randomized); (2) feasibility of randomization (75% of eligible screens randomized); (3) intervention completion (34/40, 85% of randomized individuals completing at least 1 module; average completion rates of 60% for the 16 lessons) assessed objectively via Qualtrics; (4) completion rates for midtreatment, end-of-treatment, and 2-month follow-up visits (32/40, 80% of participants completing the midtreatment visit, 30/40, 75% of participants completing the end-of-treatment visit, and 26/40, 65% of participants completing the follow-up visit).

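### The at-least-one-module benchmark does not measure self-directed uptake, because session 1 is done inside the staff-run baseline visit and still counts

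*Protocol article*

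**What the plan says.** Feasibility, including intervention completion, is a primary goal of this pilot (Protocol article, Introduction). The Feasibility Benchmarks section gives intervention completion two parts: "34/40, 85% of randomized individuals completing at least 1 module", and "average completion rates of 60% for the 16 lessons". Both are assessed from Qualtrics records.

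The Randomization and Baseline Session section fixes the order of events: "After randomization, participants will proceed to the baseline study session". That session is "also conducted over Zoom by the psychology student". At it, people allocated to the program are shown how to reach it and "will complete session 1 of the intervention as part of the visit". Only after that are they told about their 18 weeks of access.

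The Statistical Analysis section restricts the evaluation of intervention completion to the intervention arm. The target is 20 people per arm, and the Treatment Conditions section gives the control arm no access to the program. The article does not define a module separately from a lesson or session, and it does not say that session 1 is left out of the count.

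**The concern.** The program is a digital treatment meant to be used outside visits. The Strengths and Limitations section names dropout from treatment as a common problem in such studies. The first thing to learn about feasibility is therefore how many people, once left to themselves, open the program at all. A threshold of one module looks like the benchmark for that question. As written, it is satisfied before self-directed use begins.

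The stake is how the primary result will read. A statement that all or nearly all participants completed at least one module would be taken as evidence of uptake when it shows attendance at a staff-run visit. The Discussion expects the feasibility findings to set the stage for an efficacy trial, so a figure that says nothing about later use would weigh in that judgement.

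**Working it through.** **Inputs from the article.** Benchmark 34/40 = 85% with at least one module; benchmark of 60% mean completion over 16 lessons; 20 participants per arm; intervention completion evaluated in the intervention arm only; session 1 completed in the baseline visit, after randomization.

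**Assumptions.** A module is one lesson or session, as the article names no larger unit. The article gives no expected rate for completing the visit or for later use, so both are shown as ranges.

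**1. The plan's own figure.** 34/40 = 0.85, so the percentage reproduces. The denominator does not fit the analysis set: with no control access, at most 20 of 40 can complete a module, and 20/40 = 50%. Read literally, 34/40 cannot be reached. On the intervention arm, the 85% threshold is 0.85 × 20 = 17, that is 17/20.

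**2. Chance of passing as written.** Everyone who completes the visit as planned already counts. With v the proportion completing the visit, the chance of passing is P(X ≥ 17), X ~ Binomial(20, v):

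| Visit completion v | P(at least 17 of 20) |
|---|---|
| 80% | 0.411 |
| 85% | 0.648 |
| 90% | 0.867 |
| 95% | 0.984 |
| 98% | 0.999 |
| 100% | 1.000 |

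Later use of the program does not enter the calculation.

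**3. Chance of passing if a lesson after the visit is required.** With u the proportion of visit completers who do at least one further lesson, X ~ Binomial(20, u × v):

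| u | As written, v = 100% | Post-visit lesson, v = 100% | As written, v = 95% | Post-visit lesson, v = 95% |
|---|---|---|---|---|
| 0% | 1.000 | 0.000 | 0.984 | 0.000 |
| 50% | 1.000 | 0.001 | 0.984 | 0.001 |
| 70% | 1.000 | 0.107 | 0.984 | 0.059 |
| 85% | 1.000 | 0.648 | 0.984 | 0.445 |
| 95% | 1.000 | 0.984 | 0.984 | 0.876 |

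The columns for the rule as written are flat. The post-visit rule responds to uptake.

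**4. The extreme case.** If all 20 complete the visit and none returns, the one-module figure is 20/20 = 100%. Mean lesson completion is 20 × 1 / (20 × 16) = 6.25%, far below 60%.

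**5. Effect of session 1 on the 60% benchmark.** 60% of 16 lessons is 9.6. With session 1 done by everyone, lessons 2 to 16 must supply 9.6 − 1 = 8.6 of 15, or 57.3%. If q is mean completion of lessons 2 to 16, including session 1 raises the overall mean by (1 − q)/16, which at q = 60% is 2.5 percentage points.

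**6. An intermediate case.** Suppose 12 of 20 finish all 16 lessons and 8 never return after the visit.
- One-module benchmark: 20/20 = 100%, passes.
- Mean completion, all 16 lessons: (12 × 16 + 8 × 1)/320 = 62.5%, passes.
- Mean completion, lessons 2 to 16: (12 × 15)/(20 × 15) = 60.0%, still reaches the threshold.
- At least one lesson after the visit: 12/20 = 60%, below 85%.

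Only the post-visit uptake measure shows that 8 of 20 (40%) made no use of the program alone. Leaving session 1 out of the mean does not change that benchmark's result here.

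**The case against.** The strongest reply is that the two completion benchmarks stand together, and the second can catch what the first misses. That stands: a wholesale failure to return gives 6.25% against 60%. A reader might infer that the plan would support a conclusion of feasibility however little the program is used, and the article does not bear that out.

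A reader might also infer that the one-module benchmark cannot fail. That goes too far as well. Randomization comes before the visit, the denominator is randomized people, and a lesson takes 40 to 50 minutes. If 4 or more of 20 do not finish session 1, the benchmark fails. That failure would, however, tell us about the visit and not about uptake.

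A further inference concerns the benchmark of "75% of eligible screens randomized". Because "Willing and able to commit to the entire study protocol" is an inclusion criterion, one might suspect that people who decline are classed as ineligible and leave the denominator. The article does not say so. The Randomization and Baseline Session section treats eligibility and willingness to continue as two separate conditions for assignment, and on that wording an eligible person who declines still counts against the 75%. This is not part of the point.

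It can also be said that the analysis is descriptive, that no progression rule hangs on this benchmark alone, and that the 85% cut-off comes from earlier digital interventions and may not suit a stricter quantity. The last of these stands and is allowed for in the fix. None of them makes the present count a measure of uptake.

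**Conclusion.** The point holds for the at-least-one-module benchmark. As written, it measures completion of the baseline visit and carries no information on self-directed use: with full visit completion it reads 20/20 whether later uptake is 0% or 95%. The influence of session 1 on the 60% mean-completion benchmark is small (57.3% instead of 60% required of lessons 2 to 16), and that benchmark can still fail. The printed 34/40 also needs correcting, since only 20 participants have access.

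The conclusion rests on three things: a module means one lesson or session; the visit runs as described; and intervention completion is evaluated in the intervention arm, as the Statistical Analysis section states. The visit-completion and uptake rates in the tables are assumed ranges, not figures from the article.

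**What to change.** Before results are analysed:

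- Define the uptake benchmark as at least one lesson completed after the baseline visit (lesson 2 or later), with all participants randomized to the intervention arm as denominator.
- State the threshold as 17/20 in place of 34/40, or give and justify another cut-off for this stricter quantity.
- Report completion of session 1 separately, labelled as completion of the baseline visit.
- Optionally, report mean completion for lessons 2 to 16 beside the figure for all 16.

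Lesson completion is already captured in Qualtrics, so this changes definitions and wording only, with no new data and no change to what participants do. The cost is that reported uptake will look less favourable. The 85% level was set for an easier quantity: with full visit completion and a true uptake of exactly 85%, the chance of reaching 17/20 is only 0.648. The sponsor should decide on the cut-off knowing that.
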